### 2.9. Secondary Outcomes

Secondary outcomes of the study will be on the level of the infants, parents, healthcare professionals and organisation and on a possible underlying biological mechanism related to stress at parenteral level.

#### 2.9.1. Infant Outcomes

Infant outcomes include length of hospital stay, breastfeeding rates, growth, neurodevelopment at the (corrected) age of 12 months and saliva cortisol and buccal mucosal cells (see Section 2.9.5).

Neurodevelopment will be assessed using the Ages and Stages Questionnaire (ASQ, 3rd edition) [33]. With this tool, infant development can be assessed as reported by parents. The ASQ has been validated in a comparable population [34], and the validated Dutch version will be used for Dutch speaking participants [35]. The ASQ encompasses 5 domains: communicative, gross motor, fine motor, problem solving and adaptive skills. Each domain consists of 6 questions regarding the milestones that fit the age of the infant. Parents respond to the different items with “yes” (score = 10), “sometimes” (score = 5) or “not yet” (score = 0). For each domain, the score of the six items is summed, resulting in a domain score ranging from 0 to 60 and a total ASQ score with a maximum of 300 points. A positive screening is defined as scoring >2SD below the mean of the Dutch reference population in one domain, or scoring >1SD below the mean on more than one domain.

#### 2.9.2. Parental Outcomes

At discharge, parents’ experiences of the hospital admission will be evaluated in several domains. Their experience of shared decision-making will be measured by means of the Shared Decision Making Questionnaire (SDM-Q-9). This questionnaire contains 9 items, with a unidimensional structure, regarding patients’ experiences of the process of decision-making [36]. To adjust the SDM-Q-9 to a paediatric setting, “my doctor” will be replaced by “my baby’s doctor” and “my medical condition” will be changed to “my baby’s medical condition” with permission of the original authors. The SDM-Q-9 shows a good validity and reliability, with a Cronbach’s a of 0.94. Validation of the Dutch translation are in the same range, providing good reliability [37]. To be able to adjust for the preference parents may have in being involved in decision-making, the Control Preferences Scale (CPS) will be used. The CPS was originally created as a card-sorting exercise to assess the preferences an individual may have regarding the control in medical decision-making [38]. The CPS will be used in the form of a one-item questionnaire [39]. The item is answered on a 5-point Likert scale, and parents will be asked to fill out the CPS at discharge.

The CO-PARTNER tool will measure parental participation in the neonatal care and collaboration of parents with the medical team [40]. This tool can be used on the neonatal ward to describe the culture of a unit, measure the amount of FICare applied, define what parents can do in the care of their infant and in which care activities they collaborate with healthcare staff. It consists of 31 items within 6 domains: daily care (11 items), medical care (4 items), gathering information (3 items), advocacy (3 items), time spent with the infant (3 items) and closeness and comforting of the infant (7 items). Internal consistency of the domains varies from 0.558 to 0.938 and has a good convergent and divergent validity [40].

Parent–infant bonding will be measured using the Maternal Postnatal Attachment Scale (MPAS) [41]. The MPAS is a self-report tool containing 19 items with responses on a two- to five-point scale, reflecting the key experience of the mother-to-infant bond. The total score is formed by the sum of the 19 item responses. As each item score ranges from 1 (low attachment) to 5 (high attachment), to provide equal weighting of all items, the total score ranges from 19 to 95. The original version is based on a three-dimensional structure: pleasure in interaction with the infant, lack of negative feelings towards the infant, and sense of confidence and satisfaction in their competence as a parent [41,42,43]. Both the English and Dutch (translated) version show strong internal consistency [41,42]. For fathers, the Paternal Postnatal Attachment Scale (PPAS) will be used [44].

Parental mental wellbeing will be assessed longitudinally until the (corrected) age of 12 months of the infant. For this, three questionnaires will be used, sent to parents at admission (for parents of infants born <35 weeks), discharge and at the (corrected) ages of 3, 6 and 12 months of the infant. The subjects of mental wellbeing measured are stated below.

Post-traumatic stress symptoms will be assessed using the PCL-5. The PCL-5 is a diagnostic tool for post-traumatic stress disorders, adjusted to the DSM-5 [45,46]. The PCL-5 contains 20 items in a 4-factor model based on symptom clusters: intrusion, avoidance, negative alterations of cognitions and mood, and alterations in arousal and activity. The original (English) version shows a good internal consistency with a Cronbach’s a of 0.94, and has been validated in parents with satisfactory psychometric properties [47]. The PCL-5 has been translated to Dutch [48], and the translated tool shows an internal consistency similar to the original English version [49].

Depression and anxiety in parents will be measured using short forms from the PROMIS item bank. The PROMIS (Patient-Reported Outcomes Measurement Information System) item banks have been developed using both qualitative and quantitative approaches, aiming to develop more efficient PROMs that are valid, reliable and responsive [50]. The short forms contain fixed items chosen from an item bank of 6–121 items all measuring the same construct. The anxiety and depression short forms consist of 8 items each, and both show excellent internal consistency [51]. The scores of short forms are expressed in T-scores, which are standardised scores with a mean of 50 and a standard deviation of 10. The higher the (T) score, the more symptoms a parent experiences.

Outcomes at patient level (parents and infants) are listed in Table 1. Biological samples will be obtained as described under Section 2.9.5.

#### 2.9.3. Outcomes at Cluster Level

Outcomes for healthcare professionals include work engagement, autonomy and experiences in shared decision-making. The measurements of these outcomes are performed as follows.

As shared decision-making is a bidirectional process, in which both the patient and healthcare professional are involved, the healthcare professionals’ experience of the shared decision-making process will be measured. The SDM-Q-Doc, an adjusted version of the SDM-Q-9, will be used for this purpose. Similar to the version for patients (parents), the SDM-Q-Doc has 9 items in a unidimensional structure, and shows a good internal consistency with a Cronbach’s a of 0.88 [60]. The SDM-Q-Doc has been translated into Dutch [37]. To adjust the SDM-Q-Doc to our paediatric setting, “my patient” will be replaced by “the parent(s) of my patient”.

Although work pleasure is not equal to work engagement, engagement can be measured as an indicator for work pleasure. For this study, work engagement in healthcare professionals will be measured using the shortened version of the Utrecht Work Engagement Scale (UWES) [61]. The UWES-9 has 9 items (such as “At my work, I feel bursting with energy”) based on 3 subdomains (vitality, absorption and commitment). All items are scored on a 7-point frequency rating scale ranging from 0 (“never”) to 6 (“always”) [62]. The UWES-9 shows excellent internal consistency, with a Cronbach’s a of 0.93 [63].

By using the decision authority subscale of the Job Content Questionnaire (JCQ) [64], healthcare professionals’ autonomy will be assessed. The JCQ is a questionnaire with 24 items regarding aspects of work satisfaction, such as support by supervisors and work stability. The decision authority is a subscale that consists of 3 items (such as “My job allows me to make a lot of decisions on my own”), scored on a 4-point Likert scale (from “strongly disagree” to “strongly agree”) with which participants indicate at what level they agree with the statement. The total score in the subscale ranges from 3 to 12, with higher scores indicating more feelings of autonomy.

Organisational outcomes are duration and frequency of rounds, parental presence at rounds and cost-effectiveness. Outcome levels for healthcare professionals and organisations will be measured at start, halfway through and at the end of the study.

All outcomes at cluster level (healthcare professionals, cost-effectiveness) are listed in Table 2.

#### 2.9.4. Cost-Effectiveness

Cost-effectiveness will be analysed at the level of families (medical and productivity costs), organisations (work absence, length of infant’s hospital stay, hospital care costs) and healthcare professionals (productivity costs).

The social aspect of cost-effectiveness will be assessed by both the Productivity Cost Questionnaire and the Medical Cost Questionnaire of the institute for Medical Technology Assessment (iMTA PCQ and iMTA MCQ) [58,59]. The questionnaires will be slightly adjusted to fit the paediatric setting, and parents will be asked to fill out these questionnaires at the (corrected) age of 12 months of their infant. Healthcare professionals will be asked to fill out the iMTA PCQ at start, halfway through and at the end of the study.

#### 2.9.5. Biomarkers

To assess the effect of FICare on the stress hormone levels in human milk, samples of human milk will be collected at discharge and at the (corrected) age of 3 months of the infant. Mothers are requested to collect their milk from the first feeding moment in the morning at two timepoints. They are instructed to empty one breast in the morning before feeding their child. After mixing the milk, 2–10 mL will be donated in a sterile container that is provided and subsequently the collected human milk will be stored in the refrigerator at 2–8 °C. The composition (including macro- and micronutrients), immunological factors (ELISA analysis) and cortisol levels (LC-MS/MS) in human milk will be analysed.

To analyse the effect of FICare on the physiological stress response, cortisol levels in parents and infants will be assessed. Salivary samples will be collected at the (corrected) age of 3 months of the infant. On the measurement day, two samples of saliva (S1 and S2) are collected: one in the morning and one in the evening. The saliva is collected by chewing for 1 min on a swap (Salivette, Sarstedt, Rommelsdorf, Germany). S1 is obtained within 15 min after awakening in the morning, S2 is obtained before going to bed. By collecting two samples, we will make sure the cortisol day curve is captured. For infants, samples will be collected by parents before a feeding, by using a saliva swab designed for use in infants (Oracol Plus, Malvern Medical Developments, Worcester, United Kingdom). Salivary cortisol levels will be analysed by using isotope dilution liquid chromatography–tandem mass spectrometry (LC–MS/MS) [57,65].

Buccal mucosa samples of infants will be collected at discharge, and at the (corrected) age of 3 months by brushing a swab along the buccal mucosa [66]. Glucocorticoid receptor methylation rate will be analysed using the Mquant method [55].

The hair cortisol concentration (HCC) reflects long-term integrated cortisol levels, i.e., cortisol production over a prolonged period. As such, it is an index of chronic stress. Parents will be asked to collect hair samples by themselves at the (corrected) age of 3 months of the infant. Hair samples will be collected carefully with scissors as close as possible to the scalp at the posterior vertex of the head, since it has been found that this area of the scalp has the greatest growth cycle synchrony and exhibits the lowest intra-individual variability in HCC [67]. Approximately 100 hairs will be sampled. Cortisol and cortisone concentrations will be determined from the 1–3 cm segment of hair, representing hair growth over a 3-month period [68]. Hair samples will be analysed using a column switching LC–APCI–MS/MS assay [69].

### 2.10. Statistical Procedures

#### 2.10.1. Sample Size Calculation

Based on previous research, a mean difference of 13 points (0.5 standard deviations) on the total score of the PSS:NICU is expected between the intervention and control groups after implementation of FCR and FICare [25,26]. The stepped-wedge design will have a total of 7 steps of 3 months each. At each step, two hospitals will implement the FICare intervention. One step will be an implementation (or wash-out) period. With an expected amount of 25% missing data, a power of 80%, intra-cluster correlation of 0.01 and an eta of 0.5 times the estimated effect, we aim to include 600 infants and their parents divided over 10 clusters.

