### 2.2. Design

Due to the nature of the intervention, which involves changes to unit-level provision of care (medical rounds) and interaction between participants, there is a risk of cross-contamination. Therefore, to avoid contamination of patients and staff, the stepped-wedge cluster-randomised controlled trial design was selected. The trial is designed according to the CONSORT 2010 guidelines for stepped-wedge cluster-randomised controlled trials [28]. Randomisation will be performed using a random number generator, which will randomly assign the timing of start of intervention between sites. Hospitals will be stratified by level of care delivered (post-intensive care or not). The program will generate a series of blocks of varying sizes for each stratum and allocate units a time for intervention (3, 6, 9, 12 or 15 months, respectively) as is visualised in Figure 1.

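### On the conventional reading of the stated inputs, 600 infants with 25% missing data give about 72% power, not 80%; the 25% loss appears not to have been applied

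*Protocol article*

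**What the plan says.** Section 2.10.1 of the protocol article gives these inputs:

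- Effect: "a mean difference of 13 points (0.5 standard deviations) on the total score of the PSS:NICU", which implies an SD of 26.
- Layout: "The stepped-wedge design will have a total of 7 steps of 3 months each", and "At each step, two hospitals will implement the FICare intervention". With 10 hospitals this makes five sequences.
- Implementation: "One step will be an implementation (or wash-out) period".
- Loss and power: "With an expected amount of 25% missing data, a power of 80%, intra-cluster correlation of 0.01".
- Correlation and heterogeneity: "intra-cluster correlation of 0.01 and an eta of 0.5 times the estimated effect".

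From these it sets a target of 600 included infants and their parents. Missing data and power appear together as inputs to that target, so 600 reads as the number enrolled, with the loss already allowed for.

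Section 2.10.2 specifies a mixed model with hospital as a random effect and step as a fixed effect. Section 2.2 says that the program will "allocate units a time for intervention (3, 6, 9, 12 or 15 months, respectively"). Section 2.5 places a three-month implementation period before the intervention period.

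The article gives no significance level or sidedness. It does not say whether eta is an SD or a variance. It does not say whether one or two parental scores per infant enter the primary analysis, or whether families recruited during implementation count towards the 600.

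**The concern.** The article prints a power figure with nearly all the inputs needed to check it. On their ordinary meaning, those inputs give about 80% only when all 600 infants have an analysed outcome. If a quarter of outcomes are missing, as the article itself expects, the chance of missing a true 13-point difference is about 28% rather than 20%. A null primary result read against 80% power would then count as stronger evidence of no effect than it is.

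**Working it through.** **Inputs from the article.** Effect 13; SD 13/0.5 = 26, so total variance 676; intra-cluster correlation (ICC) 0.01; eta 0.5 × 13 = 6.5; 10 hospitals, two per sequence; seven periods; 25% missing.

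**Assumptions, because the article is silent.** Two-sided 5%; eta is the SD of the hospital-specific intervention effect; one score per infant; equal cluster-period sizes; no correlation between hospital intercept and hospital effect; the implementation quarter follows the stated start time and is not analysed.

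**Model.** Each cluster-period mean has a fixed period effect, a random hospital intercept, a random hospital-specific intervention effect and sampling error:

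- intercept variance = 0.01 × 676 = 6.76
- intervention-effect variance = 6.5² = 42.25
- residual variance of a cell mean = 0.99 × 676 / m = 669.24 / m, with m infants per cell

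For each hospital, V = (669.24/m) I + 6.76 J + 42.25 xxᵀ, where I is the identity matrix, J the all-ones matrix and x the 0/1 intervention indicator over the analysed periods. With Z the design matrix of period effects and x, the information matrix is the sum of Zᵀ V⁻¹ Z over the 10 hospitals. The standard error (SE) is the square root of the treatment element of its inverse. Power = Φ(13/SE − 1.96).

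**Cells.** 10 × 7 = 70 cluster-periods, less 10 implementation cells, leaves 60.

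**The plan's own figure.** With 600 analysed, m = 600/60 = 10 and SE = 4.61. Power = Φ(13/4.61 − 1.96) = 80.6%. The smallest number analysed that gives 80% is 588. The printed 80% is therefore reproduced, but with no missing data.

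**With the stated loss.** 600 × 0.75 = 450 analysed, m = 7.5, SE = 5.12. Power = Φ(13/5.12 − 1.96) = 71.8%. The difference detectable with 80% power is (1.960 + 0.842) × 5.12 ≈ 14.3 points, or 0.55 SD.

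**Other readings, each with 450 analysed and one input changed:**

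| Reading | Power |
|---|---|
| Conventional | 71.8% |
| One-sided 5% | 81.4% |
| Eta as a variance of 6.5 | 80.3% |
| Eta ignored | 82.4% |
| Implementation quarter analysed as control / as intervention (450 over 70 cells) | 82.4% / 83.3% |
| Both parents' scores, couple correlation 0.3 | 84.4% |
| Both parents' scores, couple correlation 0.5 | 80.6% |
| Both parents' scores, couple correlation 0.7 | 76.9% |
| Implementation quarter placed before the stated start time | 72.9% |

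For two parents, the residual variance per family is multiplied by (1 + r)/2, with both scores present in all 450 families. The couple correlation r is assumed; the article gives none.

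**If the 600 also covers implementation-quarter families.** 450 × 60/70 ≈ 386 analysed, SE = 5.43, power 66.8%. The article does not say that this is so.

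Taking 26 as the residual rather than the total SD changes little: 80.3% with 600 analysed and 71.5% with 450.

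**The case against.** The strongest reply is that the deciding inputs are not in the article. No alpha or sidedness is given, and the hypothesis is directional, so one-sided 5% cannot be ruled out. Eta is undefined. The target is for infants and their parents, consent is sought from both, and parents complete the stress scale, so two scores per infant are plausible. Any one of these changes can bring power with 450 families to about 80% or more, although the two-parent route falls short at a couple correlation of 0.7. The article also condenses a fuller protocol that may settle these points.

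This stands against a stronger reading that a reader might infer: that the trial certainly lacks 80% power, or that it must enrol 588/0.75 = 784 infants. The documents support neither.

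The reply does not remove the point. A superiority hypothesis does not by itself imply a one-sided test, and two-sided 5% is the usual default. Eta is expressed as a fraction of the effect, so it is in scale points and reads naturally as an SD; a variance equal to half the effect mixes units. The two-parent reading needs a couple correlation that the article does not give and a family random effect that Section 2.10.2 does not list. Ignoring eta contradicts a stated input, and analysing the implementation quarter as full control or intervention data sits badly with calling it a wash-out. Multiple imputation would not be expected to restore the information lost with missing outcomes.

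A reader might also quote 67% as the trial's power. That figure depends on implementation-quarter families being inside the 600, which nothing in the article states.

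**Conclusion.** The printed power is not reproduced on the ordinary meaning of the printed inputs: about 72% rather than 80%, a type II error of about 28% at 13 points. That 600 is exactly 10 infants in each of 60 analysed cells, at about 80% power with no loss, suggests that the 25% was listed but not applied. This is an inference, not something the article says.

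The conclusion rests on two-sided 5%, eta as an SD of 6.5 points, one score per infant, equal cell sizes and exclusion of the implementation quarter. The arithmetic is firm under those assumptions. Which assumptions the sponsor used cannot be settled from the article.

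The start times are a smaller matter. Section 2.2 attaches months 3 to 15 to the intervention, while Section 2.5 puts three months of implementation before it, so the text leaves open which event those months mark. The choice moves power by only about one point.

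**What to change.** Revise the paragraph in Section 2.10.1 in one of two ways:

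- Restate power for 600 enrolled with 25% missing as about 72% for 13 points (two-sided 5%), with a detectable difference of about 14.3 points at 80% power.
- Or state the alpha and sidedness, the meaning of eta and the unit of analysis under which 80% holds. If both parents' scores are the unit, name the family random effect and the assumed couple correlation, and show the range: about 84% at 0.3, 81% at 0.5 and 77% at 0.7.

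In either case, say that 600 is the number before loss, and that only control-period and intervention-period families count towards it. Reconcile Section 2.2 with Section 2.5 on whether months 3 to 15 mark the start of implementation or of intervention.

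The cost is one rewritten paragraph and one clarified sentence. The stated power may become less favourable. No extra enrolment is proposed.

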### 2.5. Procedures

All ten participating hospitals start the control phase, delivering SNC as they did prior to the study. Subsequently, randomisation will determine in which order the neonatal wards will start with the implementation of FCR according to the FICare principles. The outcomes will be measured at the individual level (parental and neonatal outcomes) and at the cluster level (healthcare professional-outcome measures, adherence to the intervention and cost-effectiveness). Given that the intervention includes active participation of parents in neonatal care and medical rounds, blinding is not possible for participants and researchers. However, as the outcomes cannot be influenced by the researcher and are unlikely to be influenced by the parents’ knowledge of the intervention, the risk of performance and detection bias is assumed very low.

In the three months preceding the intervention period (the implementation period), FCR and FICare principles will be implemented on the neonatal wards of the participating hospitals. We will develop and use a universal implementation strategy of FICare, adjusted to the Dutch setting, in close collaboration with the Dutch neonatal parent and patient advocacy organisation (Care4Neo). To ensure feasibility and sustainability of the intervention in all participating sites, an FICare-working group will be formed at each site. Each participating centre is responsible for the recruitment of participants of their own FICare-working group. To achieve the broadest possible representation, FICare-working groups will include neonatal nurses, paediatricians, veteran parents and other neonatal healthcare professionals (such as psychologists or physiotherapists). Veteran parent(s) will be recruited through the patient organisation (Care4Neo) or via the outpatient clinic by paediatricians. Training and guidance of the veteran parents will be coordinated by Care4Neo. The FICare-working group will be responsible for tailoring the intervention to the specific neonatal ward, in cooperation with the research team, and the planning and execution of the staff and parent training.

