#### 2.10.2. Statistical Analysis

All analyses will be performed based on an intention-to-treat principle to minimise attrition bias. A sensitivity analysis with a per protocol analysis, including, for instance, only the infants and families who have not been transferred from the study site to another hospital before discharge home, will also be performed. Possible bias due to differential withdrawal or study drop-out will be assessed in this per protocol sensitivity analysis as well. We will consider performing a subgroup analysis based on clinical characteristics, to adjust for differences in (severity of) infants’ medical conditions.

Baseline characteristics of the intervention and control group will be compared using student *t*-tests for continuous normally distributed variables, and Chi-square tests for categorical variables. Non-parametric tests will be used for variables that do not follow a normal distribution. Missing data will be handled by multiple imputation chain equations (mice) [70] with adjustment for clustering [71]. Rubin’s rules will be applied to pool the results of the different imputed dataset [72]. As described and proposed by the Panel on Handling Missing Data in Clinical Trials, we will carry out sensitivity analyses with different missing data strategies adjusted for clustering [73]. We will consider missing completely at random, missing at random, and missing not at random approaches.

With a generalised linear mixed modelling (GLMM) analysis, we will analyse whether parental stress at discharge is decreased after the intervention. We will include the factor “cluster” (hospital) as random effects, and “step” will be included as fixed (time) effect. In a secondary analysis, adjustment can be applied for possible confounders, such as (medical) characteristics of the infant during hospital stay. Adjustment for possible time effects will be made.

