An obvious limitation of this study is the non-blinding of participants (both parents and healthcare professionals) and researchers. The design of the study and the nature of the intervention makes for an unfeasible setting for blinding. However, the effects of the non-blinding design are expected to be very low on the patient (infant and parent) level, as researchers cannot influence the medical facts or responses given by parents. There is a possible bias introduced by not blinding healthcare professionals (as some could have been supporters of the FICare concept beforehand, influencing their judgement and responses to questionnaires), but this is also expected to be of low relevance. As the other outcomes on cluster level are all objective (such as cost-effectiveness), bias is not expected on this level.

Another point worth mentioning is the possible differences in the (quality of) execution of the intervention between hospitals. Many principles of both the FCR and the FICare rely on human factors such as the communicative and collaborative skills of the healthcare professionals. In an ideal setting, in the absence of any financial or time restrictions, a more extensive training, such as that described in Finnish studies, would be incorporated in the implementation strategy [75]. However, as it is clear that steps need to be made based on current practices and the possible positive effects of parental participation [12,25,26], we chose to work with an implementation strategy that is feasible for most hospitals regardless of size or staff shortage. The results of this trial might implicate the need for further improvement or extension of this strategy, for example, creating a “FICare-plus” strategy for high income countries’ level 2 wards, comparable to the work described by a Spanish research group [84] for level 3 settings and the work published in Canada on Alberta FICare [76].

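### The sample size appears to allow the intervention effect to differ between hospitals (eta), but the stated primary model has no random intervention effect, so its standard error is too small if eta is a between-hospital SD

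*Protocol article*

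**What the plan says.** Section 2.10.1 expects "a mean difference of 13 points (0.5 standard deviations) on the total score of the PSS:NICU", which puts the total SD at 26. Its other inputs are 80% power, "intra-cluster correlation of 0.01" and "an eta of 0.5 times the estimated effect". It continues "With an expected amount of 25% missing data" and arrives at the target: "we aim to include 600 infants and their parents divided over 10 clusters". Eta is not defined.

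Section 2.10.2 specifies a generalised linear mixed model. Its random part is a single factor, the cluster ("hospital) as random effects"), and step is a fixed time effect. The section names no hospital-by-intervention term, robust variance or small-sample reference distribution.

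Two other places bear on whether the effect may differ between hospitals. Section 2.5 makes each local working group "responsible for tailoring the intervention to the specific neonatal ward", in cooperation with the research team. The Discussion raises "possible differences in the (quality of) execution of the intervention between hospitals".

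**The concern.** In stepped-wedge sample-size work, an eta listed beside an intra-cluster correlation usually denotes the SD of cluster-specific intervention effects. Read that way, the planned variance of the effect between hospitals is 6.5² = 42.25. The intercept variance implied by the ICC is 0.01 × 26² = 6.76, so the effect variance is about six times larger. A model with only a hospital intercept leaves out the largest cluster-level component in the sponsor's own planning.

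Such a model treats the intervention effect as the same in all 10 hospitals. If it is not, the reported standard error omits real between-hospital uncertainty. What is at stake is the width of the primary confidence interval, whatever the average effect, and the error rate of the primary test when the average effect is zero but hospitals differ.

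**Working it through.** **Inputs.** From sections 2.2 and 2.10.1: 10 hospitals, two per step; seven 3-month periods; effect 13; SD 26; ICC 0.01; eta = 6.5. One implementation period per hospital is treated as excluded, which leaves 60 hospital-periods. Analysed numbers are 600 (10 per hospital-period) or 600 × 0.75 = 450 (7.5 per hospital-period). Assumption, because the article does not state it: two-sided 5% level.

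**Model.** Let x = 1 under the intervention. A score in hospital i and period j is β_j + θx + a_i + b_i·x + e, with Var(a) = τ² = 6.76, Var(e) = σ² = 676 − 6.76 = 669.24 and Var(b) = η². For n scores per hospital-period, the covariance of one hospital's period means is

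V = (σ²/n)I + τ²J + η²xx′.

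Let V₀ be the same matrix with η = 0, and Z the design matrix for steps and intervention.

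- SE reported by the intercept-only model: from (ΣZ′V₀⁻¹Z)⁻¹.
- Its true SE: from (ΣZ′V₀⁻¹Z)⁻¹(ΣZ′V₀⁻¹VV₀⁻¹Z)(ΣZ′V₀⁻¹Z)⁻¹.
- SE with the random intervention effect included: from (ΣZ′V⁻¹Z)⁻¹.

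**The plan's own figure.** Power is Φ(13/SE − 1.96), using the SE from the model that includes the random intervention effect.

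- SD reading, 600 analysed: SE 4.61, power 80.6%. The number required is 588.
- SD reading, 450 analysed: SE 5.12, power 71.8%. Restoring the 25% loss would need 588/0.75 = 784 included.
- Variance reading (6.5 points², SD 2.55), 450 analysed: SE 4.62, power 80.3%.

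The SD reading therefore gives 80% if the loss was not applied, and the variance reading gives 80% if it was. Power alone does not settle what eta means. Units favour the SD: half of an effect in points is in points, whereas a variance would be in points squared.

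**Large-sample error of the intercept-only model, eta = SD 6.5.** Type I error is 2Φ(−1.96 × reported SE / true SE).

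| Analysed | Reported SE | True SE | Ratio | Type I error |
|---|---|---|---|---|
| 450 | 4.50 | 5.28 | 0.853 | 9.5% |
| 600 | 3.95 | 4.77 | 0.828 | 10.4% |

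The standard error is 15% and 17% too small. A nominal 95% interval covers about 90.5% and 89.6%, and this coverage does not depend on the average effect. Other readings of the design, such as no implementation gap, give type I errors of 9.0–11.0%.

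**Sensitivity to eta (450 / 600 analysed).** Variance reading: 5.7% / 5.8%. SD 3.25: 6.1% / 6.3%. SD 9.75: 14.9% / 16.9%.

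**Simulation with estimated variances (REML, z-test, average effect zero).** The intercept-only rows use 20,000 runs and the last row uses 6,000.

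| Model and truth | 450 | 600 |
|---|---|---|
| Intercept only, eta = 0 | 5.6% | 5.8% |
| Intercept only, eta = 6.5 | 8.0% | 8.6% |
| Intercept only, eta = 6.5, unequal hospital sizes | 8.6% | 9.1% |
| Random intervention effect added, eta = 6.5 | 5.9% | 6.6% |

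The rates for eta = 0 show that 0.6–0.8 of a point above 5% (up to 0.9 with unequal hospital sizes) comes from using a z-test with 10 hospitals. The rest comes from the omitted term. With the random intervention effect and a t reference on 8–9 degrees of freedom, the rate is about 3%.

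**The case against.** - **The article does not say intercept only.** It says random effects, in the plural, and it is a condensed article whose full analysis plan is not shown. A reader might infer that the sponsor has definitely fixed an intercept-only analysis; the text does not go that far. It does state the random part of the primary model, and hospital is the only factor in it. A statistician following that sentence would leave out the term that eta stands for.
- **Eta is undefined.** This stands. Under the variance reading the problem nearly disappears, and that reading meets 80% power after the stated loss. The units argument makes the SD more natural but does not prove it.
- **The false-positive null is special.** This also stands. A reader might infer that the error is 8–9% if the intervention does nothing. In that case eta would be zero and the model runs at about 5.6–5.9%. The higher rate needs effects that vary between hospitals and average zero, and the article scales eta to a 13-point effect. The narrow interval does not depend on that null.
- **The test is not specified.** With a t reference on 8 degrees of freedom the intercept-only model would simulate at about 4–5%. The article states no such reference, and a generous critical value would offset the wrong standard error without correcting it.
- **Variation is possible, not predicted.** The Discussion speaks of possible differences, and section 2.5 describes a universal strategy. Both are compatible with heterogeneity; neither gives its size. The size comes only from eta.

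**Conclusion.** The sizing section carries a parameter that most naturally lets the intervention effect vary between hospitals, and the stated primary model has no counterpart to it. If eta is an SD of 6.5 points, the reported standard error is about 15–17% too small. Type I error for a zero average effect with varying hospital effects is then about 8–9% in simulation (9.5–10.4% in large samples), against 5.6–5.9% with eta = 0. If eta is a variance of 6.5, the large-sample error is only about 5.7–5.8%.

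These figures assume a two-sided 5% z-test, an excluded implementation period and one score per analysed unit. A reader might expect a larger error if both parents' scores are analysed. The article gives no within-couple correlation from which to size that, so no such figure is relied on here.

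**What to change.** 1. Define eta in section 2.10.1, with its units.
2. Write the primary model as fixed step and fixed intervention, with a random intercept and a random intervention effect by hospital, fitted by REML.
3. Test the intervention effect with a Kenward-Roger or Satterthwaite reference. The random effect alone is not enough, because with a z-test it still runs at about 6–6.6%.
4. Keep the intercept-only model as a named sensitivity analysis, and fix this choice before outcome data are examined.
5. Restate the power under the chosen definition of eta and the 25% loss.

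Data collection does not change, but there is a cost. The interval widens: the model SE rises from 4.50 to 5.12 at 450 analysed and from 3.95 to 4.61 at 600. The small-sample test is conservative, at about 3% with 8–9 degrees of freedom. Under the SD reading, power by z-test is about 81% if 600 are analysed and about 72% at 450. With a t reference on 9 degrees of freedom, simulated power falls to about 71% and 61%. A reader might assume that the planned sample size already absorbs the wider standard error; that holds only with 600 analysed and a z-test.
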